### **3.6 Variables**

#### **3.6.1 Dependent Variable**

The primary outcome of this study is:

- i. The changes in the means score of knowledge on occupational safety and health at food premises.
- ii. The changes in the means score of attitudes towards occupational safety and health practices at food premises

The secondary outcome of this study is:

- iii. The changes in means score of safe practices at food premises from baseline to endpoint and,
- iv. The maintenance of knowledge, good attitude, and safe practices at work from baseline to endpoint.

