### **1.5.2 SPECIFIC OBJECTIVE**

The specific objectives of this study are:

1. To describe the baseline sociodemographic, socioeconomic, working experience, training attendance, and means KAP score of food handlers.
2. To develop and implement a theory-based intervention module for food handlers in Selangor, Malaysia.
3. To evaluate the effectiveness of the SCT constructs as the main framework of the intervention module in improving KAP among food handlers between the intervention and control group.

4. To describe and compare the effectiveness of the TRIM-OSH on the change of knowledge, attitude and practice compared to standard training among food handlers between and within groups at the end, and one-month post training, after controlling for covariates.

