#### **3.6.2 Independent Variables**

The independent variables in this study:

A theory-based intervention module that being developed and implemented to examine on its effects on improving KAP score and maintaining good KAP score among food handlers attending the programme.

Covariates:

- I. Sociodemographic factors (age, gender, ethnicity and level of education)
- II. Working experience (number of years in labor force, and previous employment history)
- III. Training attendance (participation in occupational safety and health training)

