### **3.9 Data collection methods**

The data collection will occur in the selected districts in Selangor, Malaysia, within a given time frame. The questionnaire will be distributed to selected respondents in the selected Food Handler Training School. All participants who agree to participate in the study will be consented by agreeing to the agreement statement prior study begins. The questionnaire will be given in the Google Form format for the participants to access the form with the response collected immediately upon completion before and immediately after training. The participants will be contacted after one-month post-training for the reassessment of the KAP score. If the accessibility of the Google Form is not available, the same questionnaire in the hardcopy format will be given and collected on the same day at all mentioned events.

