### **3.10 Data analysis**

The collected data and will be analyzed using IBM Statistical Package for Social Science (SPSS) version 25 involving descriptive and inferential statistics. Descriptive statistics will be used to describe the characteristics of participants. Whilst, the descriptive analysis for continuous variables with mean, mode, median and percentage will be analyzed.

The bivariate analysis of Chi-square will be used to measure associations between two categorical variables. A generalized Linear Mixed Model (GLMM) then will be conducted to determine the effects of sociodemographic factors (age, gender, ethnicity, level of education), socioeconomic (employment status, household income), working experience (duration) and previous training (training attended) on KAP on occupational safety and health at food premises among food handlers pre and post intervention within and between study groups.

In further analysis, the effects of SCT constructs component as the base of the theory-based intervention module which is behavior, individual and environment factors on KAP on occupational safety and health at food premises among food handlers pre and post intervention within and between study groups will be determined.

The effects that are going to be determined is fixed and random effects. The fixed effect is factors that the only level under consideration are continued in coding those effects. For example, both male and female genders are included in the factor sex; other examples as different ethnicities are included in the factor ethnicity group. On the other hand, the random effect is the factors where its effects are random, where they are assumed to be drawn randomly from a distribution during the data-generating process. In this study, the study sample is a random sample of the target population of food handlers at food premises and the study needs to measure KAP score of the food handlers a few times.

GLMM can incorporate both fixed and random effects. Individual's response at baseline (intercept) is allowed to differ across subjects by releasing the random effect of intercept. The change in response over time is also allowed to differ across subjects by releasing the random effect of a linear slope. By adding the random effects in the model, GLMM provides estimated parameters (fixed effect) and individual variability of these parameters around the population trend (Ellison, 2017).

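### The planned model for the KAP scores does not adjust for each participant's own pre-training score, and so gives up precision that the collected data could supply

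*Combined protocol and SAP*

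**What the plan says.** Section 3.6.1 names two primary outcomes: "The changes in the means score of knowledge on occupational safety and health at food premises" and "The changes in the means score of attitudes towards occupational safety and health practices at food premises". Change in practice score is secondary there. Under section 3.9 the questionnaire is answered with the "response collected immediately upon completion before and immediately after training", and again one month later. A pre-training score is therefore planned for every participant on every scale.

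Objective 4 (section 1.5.2) promises a comparison of the groups "at the end, and one-month post training, after controlling for covariates". The covariates appear in two places. Section 3.6.2 starts with "Sociodemographic factors (age, gender, ethnicity and level of education" and goes on to work history and past safety training. Section 3.10 adds socioeconomic factors and includes "working experience (duration) and previous training (training attended) on KAP on occupational safety and health at food premises". Neither list contains the pre-training score of the outcome being analysed.

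Section 3.10 describes how baseline enters the GLMM: "Individual's response at baseline (intercept) is allowed to differ across subjects by releasing the random effect of intercept". A random linear slope over time is added. Dummy Table F (section 4.1) has baseline as a level of Time, with no baseline covariate and no group-by-time row. That table is for self-efficacy; no such table is given for knowledge, attitude or practice. Table 5 (section 3.13) lists knowledge, attitude and practice among the independent variables for the KAP score, but does not say whether baseline values are meant.

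**The concern.** The pre-training score is normally the strongest single predictor of the later score on the same scale. A random intercept seems to take care of it, since it lets people start at different levels. But if each arm keeps its own free baseline mean, any chance difference between the arms before training is subtracted in full from the follow-up difference. Baseline adjustment subtracts only the part that carries over to follow-up. Subtracting the rest adds noise.

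At stake are the power and interval width of the knowledge, attitude and practice comparisons. Section 3.6 (Sample size) states no effect size, SD, ICC or power, so no documented margin exists to absorb avoidable variance.

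**Working it through.** **The plan's own figure.** Six per cluster, inflated for 20% attrition at three time points, is 6/0.8³ = 6/0.512 = 11.72, rounded up to 12; 20 × 12 = 240. The inflation step reproduces. The base of 20 clusters of six cannot be checked, so the loss can only be stated relative to an assumed starting power.

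**What the model estimates.** Take a mean for each arm at each time, an identity link and everyone observed at all times. The fitted means are then the observed means, whatever the random intercept and slope variances. The effect at a follow-up is the change from baseline in the intervention arm minus that in the control arm. A covariate that is constant over time, entered as a main effect, contributes equally at each time and cancels. In simulated complete data (20 clusters of six), the random-intercept estimate differed from the raw change difference by at most 5 × 10⁻¹⁵. A further check with a random slope, a cluster effect and a time-constant covariate agreed to all printed digits.

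**Variance.** With unit variance at both times and correlation rho:
- raw change: 2(1 − rho)
- adjusted for baseline: 1 − rho²
- ratio, adjusted to raw: (1 − rho²)/[2(1 − rho)] = (1 + rho)/2

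With unequal SDs s0 (before) and s1 (after), raw minus adjusted variance is s0² + s1² − 2·rho·s0·s1 − s1²(1 − rho²) = (s0 − rho·s1)², which is never negative. Equal variances set the size of the loss, not its direction.

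**Power.** Assume two-sided alpha 0.05 and 80% power on raw change. The standardised effect is 1.96 + 0.84 = 2.80, and adjusted power is Φ(2.80/√ratio − 1.96).

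| rho (assumed) | Raw | Adjusted | Ratio | Power after adjustment |
|---|---|---|---|---|
| 0.3 | 1.40 | 0.91 | 0.65 | 93.5% |
| 0.5 | 1.00 | 0.75 | 0.75 | 89.9% |
| 0.7 | 0.60 | 0.51 | 0.85 | 86.0% |
| 0.8 | 0.40 | 0.36 | 0.90 | 84.0% |

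**Check with clusters.** A simulation used 10 clusters per arm, six analysed per cluster, cluster-level tests, assumed ICC 0.02 to 0.10 and cluster autocorrelation 0.8. Power rose from about 80% to 90–92% (rho 0.3), 87–89% (0.5) and 84–86% (0.7). This is close to the formula, and slightly lower at rho 0.3.

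**Baseline imbalance.** Given a chance baseline difference d between arms, the raw-change estimate shifts by −(1 − rho)d. Simulated slopes were −0.71, −0.50 and −0.30 at rho 0.3, 0.5 and 0.7; with adjustment they were about 0. With 10 clusters of six per arm and an assumed ICC of 0.05, the SD of d is √[(2/60)(1 + 5 × 0.05)] = 0.20 outcome SD. A one-SD imbalance at rho 0.5 therefore moves the estimate by 0.5 × 0.20 = 0.10 SD. The variance of this shift, (1 − rho)² per unit variance of d, equals 2(1 − rho) − (1 − rho²). It is the precision loss above, seen from another side.

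**The case against.** The strongest reply is that the plan does not commit to a raw-change analysis. Section 3.6.1 defines an outcome, not an estimator. If baseline is a covariate, modelling change or follow-up score gives the same arm effect, so the outcome wording alone is not the fault. The estimator is the GLMM of section 3.10, which does use the baseline data. This stands: a reader might infer that baseline is ignored, and the documents do not support that.

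The equivalence with raw change is also conditional. It needs a group-by-time term, which Table F lacks; an identity link, which 3.10 does not name, while it does mention log-transformed data; and complete data, although 20% attrition per time point is expected. These limits stand too. They show that the model is under-specified, not that it adjusts for baseline. If Table F's main effects were applied literally to a KAP score, the group coefficient would average over all three times, baseline included, which is not baseline adjustment either. Table 5 might have been meant to bring baseline KAP in as a predictor, but it does not say so.

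A reader might also infer that regression to the mean biases the comparison. It does not on average, because both randomised arms regress alike: simulated estimates averaged 0.50 for a true 0.50 under both methods.

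Finally, the size rests on assumed values. If rho is 0.8, the gain is only about four points. A high rho cannot be taken for granted, however: the questionnaire is new, attitude has three items, and training falls between the scores.

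**Conclusion.** The point holds as one of efficiency and specification. As written, the plan nowhere adjusts the knowledge, attitude or practice comparison for the participant's own pre-training score, and the random intercept and slope do not do this. Under equal variances, adjustment would multiply the residual variance by (1 + rho)/2, a reduction for any rho below 1. Against 80% power on raw change, the gain is about 14, 10, 6 or 4 points at rho 0.3, 0.5, 0.7 or 0.8. None of rho, ICC or starting power is in the documents, and the exact equivalence needs the conditions stated above.

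The validity of the trial is not in question here. The comparison is unbiased over randomisations with or without adjustment, and chance imbalance between a small number of clusters is one way the precision loss shows itself, not a second harm. The change is still worth making before data are seen, because it is nearly free and removes a choice that would otherwise be left to the analyst.

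**What to change.** - **Section 3.10:** for knowledge, attitude and practice separately, take the post-training and one-month scores as the repeated responses. Include group, time, group-by-time, that outcome's own pre-training score with a slope allowed to differ by time, and the covariates already listed. Report the arm difference with its interval at each follow-up. Keep unadjusted mean changes as description.
- **Section 3.6.2:** add the pre-training score of the outcome to the covariates.
- **Table 5 (section 3.13):** state whether knowledge, attitude and practice as independent variables are baseline values.

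Constraining the arm means to be equal at baseline is an alternative in principle, but the covariate form is preferable here. Section 3.5 suggests that participants may be invited after schools have been assigned, in which case baseline differences need not be chance alone and the constraint could introduce bias.

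The cost is a few sentences and one or two degrees of freedom per outcome. Results are then read as baseline-adjusted differences rather than raw changes. No further data, participants or visits are needed.

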#### **3.6.2 Independent Variables**

The independent variables in this study:

A theory-based intervention module that being developed and implemented to examine on its effects on improving KAP score and maintaining good KAP score among food handlers attending the programme.

Covariates:

- I. Sociodemographic factors (age, gender, ethnicity and level of education)
- II. Working experience (number of years in labor force, and previous employment history)
- III. Training attendance (participation in occupational safety and health training)

#### **Part 1: Personal information.**

Consist of questions of sociodemographic data (age, gender, ethnicity and level of education), employment status, income, working experience (number of years in labor force, previous and previous employment history), and training attendance (participation in occupational safety and health training).

#### **Part 2: Knowledge on occupational safety and health among food handlers**

Consist of questions on knowledge on occupational safety and health among food handlers.

#### **Part 3: Attitude towards occupational safety and health among food handlers**

Consist of the questions on the attitude on occupational safety and health among food handlers

#### **Part 4: Practice of occupational safety among food handlers**

Consist of questions about the practice on occupational safety and health among food handlers

### 3.8 Development of theory-based intervention module

The theory-based intervention on occupational safety and health among food handlers will be developed in Malay and English under the supervision of the supervisory committee. The intervention module will be developed for food handlers using an educational intervention model adopted from SCT. The validation of the module training will be based on the review and recommendation of the panel of content experts in occupational safety and health from the Faculty of Medicine and Health Sciences, UPM, to ensure that the content is appropriate and suitable for the intervention module.

[figure not shown]

Figure 7. Schematic diagram of the development of a theory-based intervention module to improve means KAP score and maintenance of KAP among food handlers.

### **3.9 Data collection methods**

The data collection will occur in the selected districts in Selangor, Malaysia, within a given time frame. The questionnaire will be distributed to selected respondents in the selected Food Handler Training School. All participants who agree to participate in the study will be consented by agreeing to the agreement statement prior study begins. The questionnaire will be given in the Google Form format for the participants to access the form with the response collected immediately upon completion before and immediately after training. The participants will be contacted after one-month post-training for the reassessment of the KAP score. If the accessibility of the Google Form is not available, the same questionnaire in the hardcopy format will be given and collected on the same day at all mentioned events.

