As for practice, there will be suggested items rated as five-point Likert-item questions with the responses of never, rarely, sometimes, often, and always, each weighing 1–5 scores, respectively. Their self-reported practice scores of them were classified as weak (<40), acceptable (40–50), and desirable (51–60). In addition, the observed practices presented a slight correlation with the self-reported practices in a previous study (Cunha et al., 2019).

The last section included three questions about the participants’ source of information, their need for education, and how they can increase their knowledge

of this issue. Also, they were asked to comment on (a) What they most liked about the course, (b) How it could be improved, and (c) What they will do differently at work as a result of their training.

## CHAPTER 4

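### The practice score taken immediately after training cannot show changed behaviour at work; make the one-month assessment the practice endpoint

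*Combined protocol and SAP*

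**What the plan says.** Section 3.9 describes three completions of the KAP questionnaire. The first two bracket the training, "with the response collected immediately upon completion before and immediately after training". For the third, "The participants will be contacted after one-month post-training for the reassessment of the KAP score". Where Google Forms cannot be used, "the same questionnaire in the hardcopy format will be given and collected on the same day at all mentioned events", so the instrument does not change between visits.

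Practice is Part 4 of that instrument (section 3.7): "Consist of questions about the practice on occupational safety and health among food handlers". Section 3.13 says the items are "rated as five-point Likert-item questions with the responses of never, rarely, sometimes, often, and always", scored 1 to 5. The self-reported total is banded as weak below 40, acceptable from 40 to 50 and desirable from 51 to 60.

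Objective 4 (section 1.5.2) sets out to compare "the change of knowledge, attitude and practice compared to standard training among food handlers between and within groups at the end" and again at one month. The Executive Summary hypothesises KAP improvement at both times. H04 (section 1.6) is framed as no difference in KAP at post-intervention. Section 3.6.1 defines the practice outcome as change from baseline to an endpoint that it does not define.

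**The concern.** A never-to-always item asks how often a person does something at work. Training can change the true answer only once the person has gone back to work and had the chance to act differently. The second questionnaire is completed as soon as training finishes, so any movement in the practice score at that visit needs another explanation.

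The other explanations are unlikely to be equal between arms. The third module session (Intervention Module Outline) teaches intervention participants to recognise wrong practices and perform correct ones, and includes a quiz. Controls receive standard training and brochures. Participants who have just been taught the desired answers then rate themselves. Randomisation does not remove this, because the intervention itself produces it. Section 3.13 also notes that observed practice correlated only slightly with self-report in a previous study.

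At stake is the wording of the conclusion: the trial could claim improved safe practice from a visit at which the completed training had not yet been used at work.

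**Working it through.** The point turns on timing and wording, so the main check is to set the sections side by side.

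1. **Is practice measured at the immediate visit?** Yes. Part 4 belongs to the questionnaire (3.7), and the questionnaire is given immediately after training (3.9). No section exempts Part 4, rewords it as intention, or adds workplace observation.
2. **Is it tested there?** Yes under Objective 4, which names the end of training and one month separately. H04 points the same way if its timing is read with the labels in dummy Tables B to F, where post-intervention is a visit distinct from one month. Those tables cover the social cognitive theory scores rather than practice, so this is a reading of the label, not a practice table.
3. **Does another section name one month as the practice endpoint?** No. Section 3.6.1 leaves the endpoint undefined. The sample size section (also numbered 3.6) does not settle it: it counts three follow-ups after baseline, while 3.9 describes two.
4. **What lies between the first two questionnaires?** For the intervention arm, the module of three one-hour sessions: 3 × 1 = 3 contact hours. The spacing of the sessions is not stated. However they are spaced, no work can follow the completed module before the second questionnaire.
5. **What lies between training and the third questionnaire?** One month, in which participants can work. This is the only described assessment that can register behaviour after completed training.

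The plan gives no figure for the possible distortion. The scoring bands allow an illustration, assuming that the top of the highest band is the maximum score and that every item is scored 1 to 5:

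- implied number of items: 60 / 5 = 12
- lowest possible total: 12 × 1 = 12, so the scale spans 60 − 12 = 48 points
- one category upward on every item: 12 × 1 = 12 points, or 12 / 48 = 25% of the span
- one category upward on half the items: 6 × 1 = 6 points, or 6 / 48 = 12.5% of the span
- a total of 39 (weak) plus 12 gives 51 (desirable)

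The last line takes the highest weak score to the lowest desirable score, so it is the most favourable example. The calculation shows how sensitive the scale is. It does not forecast the shift.

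**The case against.** The strongest reply is that the plan already reassesses practice at one month, that section 3.6.1 makes practice a secondary outcome, and that the immediate score is only one of two looks. The first part stands: the practice outcome as a whole is not invalid. It does not remove the problem, because Objective 4 tests both times, the endpoint is undefined, and the sample size section lists practice among the targeted primary outcomes.

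A second reply is that the item wording is unknown. The questionnaire is a new instrument still to be developed, and the questionnaire appendix is not in the text available for this review. The items may carry a recall period or ask about usual practice. That is fair, but a recall period would not let the immediate score register work done after training.

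Third, controls also receive training and brochures, so some of the desirability effect may be shared. The net size and direction of the artefact are therefore unknown.

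A reader might also infer several stronger points that the documents do not support:

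- **That the true effect at this visit is exactly zero and any difference is wholly artefact.** Session spacing is not given and online delivery is listed, so some work between sessions is possible. Chance variation also contributes.
- **That the trial expects people with no job, and so no practice to report.** Table A has rows for unemployed people and students, but it is an empty template, and the inclusion criteria require participants to be working in Selangor. Having no previous experience does not mean having no current job.
- **That the immediate score contaminates an average over follow-up visits.** No section plans such an average.

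**Conclusion.** The point holds for the practice comparison immediately after training, and only there. That score cannot reflect behaviour at work after the completed training. A between-arm difference would mainly show intention, changed interpretation of the items or social desirability, and should not be reported as improved safe practice.

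The size of the distortion cannot be derived from the documents; the 12-point figure is an illustration that rests on an inferred 12 items. The conclusion itself rests on two things: Part 4 is given at the immediate visit, as sections 3.7 and 3.9 read, and its items ask about frequency of actual practice, as section 3.13 indicates. The knowledge and attitude comparisons at that visit are not affected. The one-month practice comparison remains usable, subject to the limits of self-report.

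**What to change.** Before data collection:

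1. In section 3.6.1, define the practice endpoint as change from baseline to the one-month assessment.
2. Give the practice items a stated recall period, for example the past month at work.
3. Limit the end-of-training comparison in Objective 4, and the post-intervention wording in H04, to knowledge and attitude. Align the Executive Summary with this.
4. Omit Part 4 at the immediate visit, or report it only as intended practice. In either case keep it out of the practice effectiveness model in section 3.10.
5. Keep all randomised participants in the practice comparison and report descriptively how many were not working at each assessment. Do not restrict the analysis to those working at both times: employment at one month arises after randomisation, and selecting on it could bias the comparison.

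The cost is wording changes and one practice measurement lost or demoted. No visit is added, and section 3.13 already plans to ask what participants will do differently at work, so some information on intention would remain. The change leaves the sample size as it is.
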